#### Professional and organizational level

Characteristics of general practices are assessed, including information on area, type of practice, years of establishment, age of GPs, and structure of asthma care. PN characteristics include gender, age, education, and years of experience with asthma consultations. The process evaluation contains outcomes on the adherence of professionals to the implementation strategy and can be considered as a feasibility evaluation. Attendance to training sessions of professionals is registered. Active referral of patients by professionals to PatientCoach is registered as active participation of practices. Actual treatment advice by the care provider and the treatment advice by the system are registered. Furthermore, frequency and time of IBSM usage by care providers are digitally logged.

#### Economic evaluation

The economic evaluation includes outcomes on cost-effectiveness and cost-utility. Medical costs, such as prescribed medication are assessed from electronic patient records (with written patient permission) complemented with the patient’s report on medication purchased elsewhere
[44]. In addition, actual treatment advice by the care provider and treatment advice by the system are registered. Healthcare consumption, absenteeism and productivity loss, and the number of limited activity days are measured by using the Cost Questionnaire
[34]. Furthermore, data on patient contacts (frequency of in-practice routine asthma consultations, telephone/email consultations, and unscheduled visits) are registered.

#### Analysis

The analysis is carried out on an intention-to-treat basis*.* Analyses include descriptive statistics and comparisons on process and effect evaluation. Differences are compared between implementation strategies using a random-effects analysis accounting for within-patient repeated measurements and clustering on general practice, or nonparametric comparisons, such as chi-square, as appropriate. All data are analyzed using STATA.

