#### Blinding and strategy allocation

General practices (*i.e.*, 2,300 patients per ‘standard practice’) will be the unit of randomisation. Practices will be stratified according the following characteristics: postal code (area) and practice size (practices with <4 GPs are defined as a small practice, practices with ≥4 GPs as a large practice). Prior to informed consent, practices will be randomized into one of the strategies (1:1:1 ratio), in order to assess the participation level of practices per strategy. Practices will receive a letter containing information on the allocated implementation strategy and an invitation to participate in the project.

Both practices and patients will be blinded to group allocation. Researchers will not be blinded for group allocation. Randomisation will be conducted by [name] using a computer-generated, permuted-block scheme. General practices will be invited until enough practices per strategy are participating. General practices will be enrolled by [name], [name], and [name]. Patients will be enrolled by general practices.

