#### Sample size calculation

The sample size is based on patient participation in IBSM (primary outcome). We assume that one-third of the 15% to 20% of patients who have a written action plan
[9] are actually using it to conduct self-management activities. Assuming that with the MS, 5% of the patients are frequently using the IBSM to monitor their asthma, we will consider the IS and ES successful if an increase of 25% is achieved (alpha 0.05 and beta 0.20). Using a correction for clustering of patients in practice (intra-cluster correlation coefficient: 0.25), we calculated that we need 10 patients in each of 42 practices 14 practices in the MS, IS, and ES, respectively to be invited to participate in IBSM using PatientCoach. This gives a total of 420 patients.

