#### Economic evaluation

The economic evaluation compares differences in societal costs to differences in the number of limited activity days (CEA) and quality-adjusted life years (CUA). The analysis has a six-month time horizon, without discounting. Group averages are statistically compared using two-sided bootstrapping and net-benefit analyses are used to compare costs to patient outcome. Sensitivity analyses are performed on the perspective (societal versus healthcare perspective) and the applied utility measure (Dutch EQ5D, VAS).

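### The Analysis section leaves open an unadjusted chi-square for patient-level outcomes; on IBSM participation it would carry about 28% type I error per comparison at the plan's own ICC

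*Protocol article*

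**What the plan says.** - **Method.** The Analysis section (Protocol article) names a random-effects model handling repeated measures within patients and clustering by practice, then adds "or nonparametric comparisons, such as chi-square, as appropriate". The same section says the comparisons cover both process and effect evaluation. No outcome is assigned to either method.
- **Primary outcomes.** Measurements and outcomes gives two patient-level proportions: referred patients who take up IBSM (defined through ACQ monitoring in two of three months), and patients with a clinically relevant AQLQ improvement.
- **Clustering assumed in the design.** Sample size calculation works from patient participation with "intra-cluster correlation coefficient: 0.25", and concludes "we need 10 patients in each of 42 practices 14 practices in the MS, IS, and ES, respectively".
- **Randomisation.** The practice is the unit. Blinding and strategy allocation states: "Practices will be stratified according the following characteristics: postal code (area) and practice size".
- **Economic comparison.** The Economic evaluation section that follows Analysis of clinical data states: "Group averages are statistically compared using two-sided bootstrapping". It names no resampling unit.

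**The concern.** The sample size is multiplied by 3.25 because patients in one practice are expected to resemble each other. An ordinary chi-square on patients assumes that they do not. Offering it as an alternative to the clustered model, without limiting where it applies, leaves open an analysis at odds with the design.

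The primary outcomes could plausibly be sent down that route. Each is a yes/no result per patient, whereas the random-effects model is described partly in terms of repeated measurements. Study design and Endpoint evaluation say that minimum-strategy patients are assessed only at six months (Table 4 differs for the AQLQ), so someone could argue that the repeated-measures model does not fit. Researchers are not blinded to allocation, so an undefined choice of test for a primary outcome could be made by people who know the arms.

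At stake is the false-positive rate on the outcome that sized the trial, and the width of its confidence intervals.

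**Working it through.** **Inputs (Sample size calculation).** "alpha 0.05 and beta 0.20" (sidedness not stated; two-sided assumed). Control rate 0.05: "Assuming that with the MS, 5% of the patients are frequently using the IBSM to monitor their asthma". Effect: "we will consider the IS and ES successful if an increase of 25% is achieved", read as 25 percentage points (0.05 against 0.30), the reading that reproduces the stated size. ICC 0.25; m = 10 patients per practice; 14 practices per arm.

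**Step 1: reproduce the plan's figure.** Two proportions, pooled variance under the null, mean proportion 0.175:

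n = [1.96 × √(2 × 0.175 × 0.825) + 0.842 × √(0.05 × 0.95 + 0.30 × 0.70)]² / 0.25² = 35.1, so 36 per arm, or 43 with the continuity correction.

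Design effect = 1 + (10 − 1) × 0.25 = 3.25. Then 43 × 3.25 = 139.75, so 140 per arm = 14 practices of 10, and 3 × 140 = 420, which matches. (Two-sided alpha 0.025 without continuity correction also gives 43. Either route uses the same design effect, so the point below is unaffected.)

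**Step 2: unadjusted chi-square on participation.** The true standard error exceeds the one assumed by √3.25 = 1.80. Actual type I error at nominal 5%:

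2 × [1 − Φ(1.96 / √3.25)] = 2 × [1 − Φ(1.087)] = 27.7%.

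Put differently, 140 / 3.25 ≈ 43: under this ICC, 140 patients per arm carry the information of about 43 independent ones.

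**Step 3: check by simulation.** Beta-binomial data, 14 practices of 10 per arm, ICC 0.25, no true difference, 100,000 replicates per row:

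| True proportion | Chi-square, uncorrected | Chi-square, Yates | t-test on practice proportions |
|---|---|---|---|
| 0.05 | 27.4% | 20.6% | 3.1% |
| 0.15 | 28.4% | 24.4% | 4.8% |
| 0.30 | 28.1% | 24.9% | 5.0% |
| 0.50 | 27.5% | 24.6% | 5.0% |

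Table 1 of the article gives 12 practices per strategy rather than 14. With 12 and a true proportion of 0.30, the uncorrected figure is 28.2%, so that discrepancy does not matter here. One three-arm chi-square on 2 degrees of freedom would have about 40% error: P(χ² > 5.99 / 3.25) = 39.8%.

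**Step 4: the AQLQ outcome.** No ICC is stated, so these values are assumptions, with m = 10:

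| ICC (assumed) | Design effect | Type I error |
|---|---|---|
| 0.01 | 1.09 | 6.0% |
| 0.05 | 1.45 | 10.4% |
| 0.10 | 1.90 | 15.5% |

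Ten is the number invited per practice; fewer may be analysed. With m = 5 (assumed), the design effect is 1 + 4 × 0.25 = 2.00 at ICC 0.25, giving about 17%, and 1 + 4 × 0.10 = 1.40 at ICC 0.10, giving about 10%.

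**The case against.** The strongest reply is that the plan names the right method first and offers chi-square only where appropriate. The sentence covers process outcomes too. Practice participation (the first hypothesis) is measured on the unit that was randomised, so an ordinary chi-square is valid there. The sample size calculation corrects participation for clustering, so the authors plainly had clustering in mind. A condensed article may also leave the pairing of outcome and test to a fuller document.

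Much of this stands. A reader might infer that the plan prescribes chi-square for the primary outcomes. It does not; the defect is an open choice. A reader might also apply 28% to both primary proportions. The ICC of 0.25 appears only in the participation calculation, so for the AQLQ outcome the figure would be an assumption.

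Nor do the documents support saying that the plan specifies a bootstrap ignoring practices. The text names no resampling unit, and no ICC for costs or QALYs is given from which to compute an error. Likewise, leaving the stratification factors out of a one-sentence model description is normal condensation. Including them is an inexpensive improvement in precision, not the correction of an error, and its size cannot be computed from the article.

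What does not stand is that the chi-square clause is mere silence. It is a written alternative to the clustered model, and nothing in the article limits it to outcomes for which it is valid.

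**Conclusion.** The point holds as a badly fixed choice of method. The Analysis section allows an unadjusted chi-square between strategies without excluding patient-level outcomes. Used on IBSM participation, it would have about 28% type I error per pairwise comparison, more than five times nominal, with standard errors too small by a factor of 1.80. This rests on the plan's own ICC and 10 patients per practice, an uncorrected pairwise test, and a two-sided 5% level. A Yates correction lowers it only to about 21% to 25%. For AQLQ improvement the size is unknown: about 10% to 15.5% for assumed ICCs of 0.05 to 0.10 with 10 analysed patients per practice, and lower with a smaller ICC or, at a given ICC, fewer patients. The bootstrap's resampling unit and the stratification factors are secondary clarifications, and none of these percentages applies to them.

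**What to change.** 1. State that both primary proportions and all other patient-level comparisons use the random-effects analysis already named. For binary outcomes, specify mixed-effects logistic regression with a random intercept for practice and a small-sample correction reflecting the number of practices.
2. Keep chi-square only for practice-level outcomes, such as whether a practice participates.
3. Include practice size in the model, and area where the number of areas allows. That number is not given, and at the assumed 5% the minimum strategy would have only 140 × 0.05 = 7 users, so many area terms could make the model unstable.
4. In the economic evaluation, state that the bootstrap resamples practices.

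The change is to analysis wording only; no further practices, patients or data are needed. The price is wider intervals than an unadjusted test would report: for participation at ICC 0.25 with 10 per practice, by a factor of about 1.80. The sample size already allows for this.

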#### Analysis of clinical data

The number of patients with a clinically relevant improvement in asthma-related quality of life is based on a minimal clinical importance of difference (MCID) of 0.5 for the AQLQ
[30].Patient utilities: asthma symptom utilities are obtained from the AQLQ
[42]; indirect utilities from the general public are obtained using the EQ-5D
[31,43]. This allows the calculation of quality-adjusted life years (Qalys). In the base case analysis, Qalys are estimated using societal utilities obtained using the Dutch EQ-5D tariff
[45]. For sensitivity analyses, Qalys are estimated using a VAS (transformed using a power transformation). Data on healthcare provider utilization and other related costs provide input for calculation of the contract price that GPs will have to negotiate for this improved service. Ideally, this is in the form of a primary care diagnosis and treatment standard fee.

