Therefore, the current challenge is to implement IBSM support in routine asthma management within primary care. Patients that are most likely to be willing to participate and benefit from (internet-based) self-management are those with partially controlled or uncontrolled asthma
[18-20]. These patients constitute about two-thirds of the asthma population in primary care
[8].

A structured implementation strategy is needed to incorporate IBSM in current clinical practice and subsequently into a patient’s daily life. Implementation strategies for IBSM, consisting of several components (so-called ‘multi-faceted implementation strategy’) are suggested to be more effective in changing current clinical practices
[21]. In addition, tailoring the implementation strategy to barriers and facilitators experienced by the target group—patients with asthma, practice nurses (PNs), and general practitioners (GPs)—is recommended
[22-24]. Such barriers can be identified at different levels of healthcare system
[25]: innovation, the individual patient (*i.e.*, illness perceptions), professional level, societal context (opinion of colleagues), organisational context (organisation of care process), and economic and political contexts.

Prior to this project, we conducted focus groups and interviews with patients and professionals for exploring barriers and facilitators for usage of IBSM in primary care
[26]. These barriers were identified at patient and professional/organizational level. Main barriers at the patient level were unawareness of their level of asthma control and subsequent possibility for improvement, and patients often do not perceive asthma as a chronic condition and experience difficulties of integrating self-management activities into daily life. Main barriers at the professional level (PN, GP) and organizational level were unawareness of the level of asthma control of patients, lack of structure of asthma care, and lack of structure of routine asthma consultations within general practice and lack of time. Consequently, we developed three implementation strategies (the strategies will be described in more detail below):

1. Minimum strategy (MS): dissemination of the IBSM program.

2. Intermediate strategy (IS): MS + start-up support for professionals (*i.e.*, support in selection of the appropriate population and training of professionals).

3. Extended strategy (ES): IS + additional training and ongoing support for professionals.

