**Methods**		
**Participants**	Eligibility criteria for participants and the settings where the data were collected	Eligibility criteria for general practices:
		Location within the Leiden - the Hague region. General practitioner/practice nurse that is willing and available to support patients in internet-based self-management.
		Patient eligibility criteria: Age 18 to 50 years; a doctor diagnosis of asthma; prescription of inhaled corticosteroids and/or montelukast ≥ three months within 12 months prior to enrolment; internet access; ability to understand written and oral Dutch instructions. Patient exclusion criteria: Severe co-morbidities, daily or alternate day oral corticosteroid therapy for ≥1 month prior to entering the study and being primarily under treatment by a respiratory physician.
		Data will be collected in a research module of the internet-based self-management support program (PatientCoach.nl) using web-based questionnaires (SurveyGizmo, Boulder, Colorado).
**Interventions**	Interventions intended for each group	Internet-Based Self-Management (IBSM) support program :
		PatientCoach.nl consists of both a generic web-based system and an instruction visit for patients. PatientCoach includes modules for self-monitoring (asthma control and lung function), a treatment plan (medication,), motivational feedback, e-consultation, personalized information (i.e., inhalation technique), reminders and forums for patients and professionals. PatientCoach has been developed by the LUMC. Patient Coach will be integrated in the general practice information system. Additionally PatientCoach contains a research module which consists of electronic versions of questionnaires.
		General practice level
		The implementation strategies for internet-based self-management support are primarily targeted general practices:
		1. Minimum strategy (MS): dissemination of the IBSM program.
		2. Intermediate strategy (IS): MS + start-up support for professionals (i.e., support in selection of the appropriate population and training of professionals).
		3. Extended strategy (ES): IS + additional training and ongoing support for professionals.
		All general practices will be asked to invite at least 10 patients to participate in PatientCoach. Follow-up duration at general practice level is one year.
		Patient level:

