#### Eligibility criteria patients

Patients, age 18 to 50 years, with a doctor diagnosis of asthma and prescription of inhaled corticosteroids and/or montelukast for at least three months in the previous year who have access to the internet are eligible to participate.

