#### Start-up support package

The start-up support intermediate package consists of: Practice recruitment. General practices receive an invitation letter that includes all components of the Start-up Support Implementation strategy. Non-responding practices receive a reminder letter within four weeks and if necessary, practices are phoned.

On-site support for patient recruitment. PatientCoach team members offer practices the opportunity to make a patient selection in the patient registries of participating GPs.

PatientCoach start-up training. PNs and GPs are invited for an interactive session (duration: two hours) with colleagues. In this session, professionals are stimulated to discuss with each other on how to apply IBSM in their own practice. This training is focused on a proactive attitude toward patients and supporting them in their self-management skills by using IBSM support:

1. Exploration of a patient’s knowledge about asthma, illness perceptions
[36,37], and the ability to integrate (internet-based) self-management activities into their daily life; *i.e.*, by exploring difficulties and discussing solutions.

2. Asthma control: assessment of the level of asthma control; patients are invited to discuss their most recent ACQ-score. Reasons for poor asthma control in patients are discussed, and the subsequent management strategy will be discussed.

3. Medication: information on side-effects; instruction, exploration of therapy adherence, and checking correct inhaler technique.

4. Asthma related lifestyle: smoking cessation, avoidance of triggers, regular exercise;

5. Asking about and treating rhinitis, which is known to influences asthma outcomes
[38].

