#### Measurements and outcomes

Primary outcome measures are the proportion of referred patients that participate in IBSM and the proportion of patients that have clinically relevant improvement in the asthma-related quality of life as measured by the Asthma Quality of Life Questionnaire
[30]. Patient usage of IBSM is based on monitoring of the level of asthma control using the Asthma Control Questionnaire
[28,29]; monitoring of ACQ during two out of three months ACQ-monitoring compliance.

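### The AQLQ responder comparison is open to case-mix differences between strategies, because patients are chosen after allocation with no impairment criterion and the text on selection support conflicts with Table 2

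*Protocol article*

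**What the plan says.** All places are in the protocol article.

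- **Outcome.** Measurements and outcomes names, as the second primary outcome, "the proportion of patients that have clinically relevant improvement in the asthma-related quality of life". Analysis of clinical data sets the threshold at 0.5 AQLQ points: "The number of patients with a clinically relevant improvement in asthma-related quality of life is based on a minimal clinical importance of difference (MCID) of" that size.
- **Entry.** Eligibility criteria patients asks for age, diagnosis, controller prescription and internet access: "Patients, age 18 to 50 years, with a doctor diagnosis of asthma and prescription of inhaled corticosteroids and/or montelukast for at least three months". Neither it nor the exclusion section sets an ACQ or AQLQ level.
- **Who is expected to gain.** Background says: "Patients that are most likely to be willing to participate and benefit from (internet-based) self-management are those with partially controlled or uncontrolled asthma". It adds: "These patients constitute about two-thirds of the asthma population in primary care".
- **Order of events.** Under Blinding and strategy allocation, practices are randomised before consent, receive a letter describing their strategy, and then enrol patients themselves.
- **Selection support.** Table 1 defines IS as "MS + start-up support for professionals (i.e., support in selection of the appropriate population and training of professionals", and ES builds on IS. Start-up support package describes the help: "PatientCoach team members offer practices the opportunity to make a patient selection in the patient registries of participating GPs". The Minimum strategy section lists none. Table 2, however, marks on-site support for patient selection and invitation for MS, IS and ES.
- **Baseline.** Study design and Endpoint evaluation give MS patients a six-month assessment only. Table 4 lists AQLQ and ACQ at 0 months for all strategies.
- **Comparison.** Analysis names a random-effects model for repeated measurements and practice clustering, or a chi-square type test.

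**The concern.** A patient who starts with good quality of life has little room to gain 0.5 and will mostly count as a non-responder under any strategy. A patient who starts badly has room to gain, and will also tend to score better on remeasurement through regression to the mean. The responder rate in an arm therefore depends on whom its practices invite. Randomising practices does not balance this, because patients are chosen after allocation by practices that have been told what their strategy contains.

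If two of the three strategies help practices choose patients and the third does not, the baseline mix may differ. A higher responder rate in IS or ES could then be read as better improvement in comparable patients when part of it reflects who was invited. A practice random effect changes the standard error but does not remove a baseline imbalance. A chi-square test cannot adjust for baseline at all.

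**Working it through.** **1. The plan's own figure.** Sample size calculation uses participation in the programme: 5% in MS, an increase of 25 (read as percentage points, so 30%), alpha 0.05, power 0.80, intra-cluster correlation 0.25, and 10 patients per practice.
- Two proportions, two-sided, with continuity correction: 43 per arm.
- Design effect: 1 + (10 − 1) × 0.25 = 3.25.
- 43 × 3.25 = 139.75, hence 14 practices of 10, or 140 per arm and 420 in all.

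The stated size reproduces. Sidedness and continuity correction are my assumptions; without the correction, 36 × 3.25 = 117, or 12 practices. The calculation does not involve the AQLQ outcome. The article gives no AQLQ responder rate, so what follows is an illustration.

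**2. Case mix with no strategy effect.** Let s be the share of an arm's patients who are not fully controlled, r1 their responder rate, and r0 the rate in controlled patients. Both rates are assumed the same in every arm.

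Arm rate = s × r1 + (1 − s) × r0

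Gap = (s in IS/ES − s in MS) × (r1 − r0)

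For MS, s = 2/3, from Background. That share describes the primary care asthma population, so using it for MS participants is an assumption. For IS/ES, s = 1 or 0.85 is assumed. Ranges tried: r1 from 0.30 to 0.50, r0 from 0 to 0.20.

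| s in IS/ES | smallest gap (r1 0.30, r0 0.20) | largest gap (r1 0.50, r0 0) |
|---|---|---|
| 1 | (1/3) × 0.10 = 3.3 points | (1/3) × 0.50 = 16.7 points |
| 0.85 | 0.1833 × 0.10 = 1.8 points | 0.1833 × 0.50 = 9.2 points |
| 2/3 | 0 | 0 |

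A worked case with r1 = 0.40 and r0 = 0.05:
- MS: (2/3) × 0.40 + (1/3) × 0.05 = 28.3%.
- IS/ES at s = 1: 40.0%.
- Gap: 11.7 points.

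The gap is also nil if r1 = r0.

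**3. Effect on the test.** Carrying the correlation of 0.25 over to the AQLQ outcome (an assumption), the effective size per arm is 140 / 3.25 = 43.1. In the 11.7-point case, a two-sided 5% test would favour IS/ES in about 20% of trials, against 2.5% with equal case mix. At s = 0.85 with the same rates, the gap is 0.1833 × 0.35 = 6.4 points and the figure is about 9%.

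**4. Can the imbalance be adjusted for?** Under Study design and Endpoint evaluation, MS has no baseline AQLQ. Then neither a 0.5 change nor an adjustment can be computed in that arm. Under Table 4, both can. The outcome itself therefore already needs Table 4 to be right for AQLQ; adjustment adds only baseline ACQ, which Table 4 also lists for all strategies.

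**The case against.** The other side has five fair points.

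- **MS may receive the same help.** A reader of the strategy definitions might infer that MS practices choose patients unaided. Table 2 says otherwise. If Table 2 is right, the main route to a difference largely disappears. The document conflicts with itself, so the stronger claim cannot be made.
- **Selection may not track impairment.** A reader might infer that IS and ES select patients who are able to benefit. No section says so: the support is a registry search, which may only apply the entry criteria. The inference is plausible, because professionals' unawareness of asthma control is a named barrier, IS was built to address such barriers, and IS training covers assessing control. It remains an inference.
- **Selection is part of what is tested.** The Implications section lists the support needed to identify eligible patients among the things the study may inform. Better targeting is then partly a strategy effect, and calling the whole gap spurious would go too far. Regression to the mean, however, is no benefit on any reading.
- **Covariates may sit in an analysis plan that is not shown.** This is accepted, and their absence from the article is not counted. What stands is that the design creates the need, and that the chi-square option cannot meet it.
- **Broad entry suits an implementation trial.** This is also accepted. The point does not ask for an impairment criterion at entry.

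**Conclusion.** The point holds conditionally. A responder outcome based on change, entry without an impairment criterion, and patient choice after allocation together allow responder rates to differ between strategies through case mix and regression to the mean. The comparisons named in Analysis would not correct it. Whether selection actually differs by arm cannot be settled until the strategy text and Table 2 agree.

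The size is unknown. Under assumed response rates it runs from 1.8 to 16.7 points, and it is nil if case mix is equal. These figures, and the 20% in the worked case, show that the effect can matter; they do not predict a bias in this trial. The participation sample size is unaffected.

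The contradiction over the MS baseline is the more basic defect, because the outcome cannot be computed in MS without that measurement.

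**What to change.** 1. Reconcile Study design and Endpoint evaluation with Table 4, and state whether MS patients have AQLQ and ACQ at 0 months. Reconcile the strategy text with Table 2 on selection support, and state what the selection is based on.
2. With the baseline confirmed, compare AQLQ responders between strategies in the practice-clustered random-effects model, with baseline AQLQ and ACQ as patient-level covariates, and not by chi-square.
3. Report the unadjusted comparison beside it, labelled as the effect of the strategy as a package including its selection component. Report baseline AQLQ and ACQ by arm.
4. Optionally, add a supportive analysis in patients outside the protocol's controlled range (ACQ above 0.75). This group should not be called not controlled: the protocol keeps that term for 1.50 or more and leaves the values between unlabelled.

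**Cost.** If Table 4 holds, this is analysis wording, with no new patients or measures. If the six-month-only text holds, MS needs a baseline measurement, and that adds research contact in an arm where the Discussion says it is deliberately kept low. Baseline is taken after allocation, so adjustment may remove the part of a strategy's effect that works through better targeting; both estimates are reported for that reason. Adjustment also deals only with measured differences. The supportive analysis would use roughly two thirds of patients if the Background share applies.
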